To date, only one randomized controlled trial (RCT), namely Sharda et al. (29), has integrated both behavioral outcomes and functional brain connectivity to evaluate the effects of music interventions on school-aged children with autism. Sharda et al. selected six target seed areas (bilateral Heschl’s gyrus, HG; inferior frontal gyrus, IFG; temporal pole, TP) based on their relevance to language and communication, as well as a prior study on perception of sung versus spoken words (44). The findings from the seed-based connectivity analysis indicated an increase in connectivity between auditory seeds (left and right HG) and striatal and motor regions, as well as a decrease in connectivity between auditory seeds (left HG and right TP) and visual areas following 8–12 weeks of music intervention compared to a non-music play-based intervention. Importantly, these changes in connectivity were correlated with improvements in social communication scores as rated by parents, providing initial evidence that music interventions can improve both social communication and functional brain connectivity in children with autism (29). However, there is a need for replication and expansion of these findings, and this is the aim of the Music for Autism (M4A) trial.

The M4A trial will investigate various additional outcomes and potential mechanisms than those studied by Sharda et al. These include exploring the impact of MT on chronic stress, an often overlooked issue among individuals with ASD (10) that has been shown to impede learning (45) and that can be modulated through musical interventions (46). The study will also examine potential structural brain changes, which are known to be influenced by psychological and biological therapies (47) as well as musical training (48). Furthermore, the research will delve into the concept of predictive processing, exploring potential links between prediction and pleasure derived from music (49), and it will examine children’s participation in the community, which is known to be limited by environmental barriers (50). Lastly, brain structure and function are closely tied to the gut microbiome (i.e., the microorganisms that inhabit the gastrointestinal tract) (51). The study aims to both examine the gut-brain axis in children with ASD (52, 53) and to explore whether music therapy intervention could serve as a potential modulator of effects.

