### Aims

1.1.

The primary aim of the Music for Autism (M4A) trial is to investigate whether a 12-week music therapy intervention, compared to play-based therapy, can lead to improvements in social communication and functional brain connectivity in school-aged children with autism. Secondary aims include examining the effects of MT on a range of psychometric, neuroimaging, and biological outcomes in children with autism.

We hypothesize that a 12-week music therapy (MT) intervention, compared to play-based therapy (PT), will lead to the following outcomes in children with autism aged 6–12:

1. Psychometric outcomes:

Significant improvements in *social communication* (primary).Increased *participation* in home, school, and community life.Improvements in *family quality of life*.Increased *adaptive behaviors*.Improvements in *receptive vocabulary* skills.Improvements in *social functioning*.Improved *prediction* accuracy.

2. Neuroimaging outcomes:

Changes in *resting-state functional connectivity* (primary), characterized by:Increased coupling between auditory and both striatal and motor regions.Decreased coupling between auditory and visual regions.Increased whole-brain *grey and white matter volume.*

3. Biological outcomes:

Reduced hair cortisol concentration, indicating a decrease in *chronic stress*.Alterations in *gut microbiome* composition and an association between changes in gut microbiome composition and changes in neuroimaging and psychometric outcomes.

Furthermore, we anticipate that the observed changes in functional connectivity will correlate with the primary outcome of improved social communication skills.

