#### Neuroimaging data analysis

2.7.3.

Resting-state fMRI data will be preprocessed prior to statistical analysis. Preprocessing steps will include realignment with correction of susceptibility distortion interactions, slice timing correction, outlier detection, direct segmentation, normalization to MNI, and smoothing. We will examine the quality of fMRI scans using visual inspection and framewise displacement (FD) (83), an indicator of head motion, which is a common problem especially in children and clinical populations (84). Volumes exceeding a certain FD threshold [0.5 mm (83) or other values (85)] can be down weighted or scrubbed to obtain usable data (83); longer passages of high movement can be removed.

To examine resting-state functional connectivity (RSFC), the timeseries for each of the six seeds selected will be regressed against all other voxels timeseries in the brain to generate individual participant-level connectivity maps, using whole-brain general linear models at baseline and after the interventions. These first-level maps will then be entered into the second-level analyses. For comparison after the intervention, we will use ANCOVA with post-intervention RSFC as a dependent variable, and intervention, baseline RSFC, age, and IQ as covariates. Z-scores of parameter estimates will be used to measure connectivity strength. Results will be reported with a 5% significance level adjusted for multiplicity by familywise error rate.

To examine the relation between RSFC and behavior change, Z-statistics for each participant from the post-intervention RSFC maps will be used in a linear regression model to evaluate correlation between RSFC and behavior change. All tests will use a two-sided 5% significance level. The two main secondary psychometric outcomes, participation, and quality of life will be Bonferroni-corrected; the remaining secondary outcomes will be exploratory.

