Finally, it is important to note that the power calculations for the M4A study were conducted for the primary outcomes, so analyses involving secondary outcomes, relationships between biomarkers and psychometric outcomes, and clinically defined subgroups will be considered exploratory.

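### The brain-behaviour regression uses post-intervention connectivity level, while the hypothesis concerns change in connectivity, so it is a diluted and confounded test of that hypothesis

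*Protocol article*

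**What the plan says.** All references are to the protocol article.

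- **Section 1.1 (Aims)** closes with the hypothesis: "we anticipate that the observed changes in functional connectivity will correlate with the primary outcome of improved social communication skills".
- **The Introduction** describes the earlier trial's result, which this trial sets out to replicate, in the same terms: "these changes in connectivity were correlated with improvements in social communication scores as rated by parents".
- **Section 2.7.3 (Neuroimaging data analysis)** gives the brain-behaviour analysis in one sentence. Its purpose is "To examine the relation between RSFC and behavior change", and its method is "Z-statistics for each participant from the post-intervention RSFC maps will be used in a linear regression model to evaluate correlation between RSFC and behavior change". No baseline connectivity term is named.
- **The preceding paragraph of 2.7.3** produces connectivity maps "using whole-brain general linear models at baseline and after the interventions". For the treatment comparison it specifies "ANCOVA with post-intervention RSFC as a dependent variable, and intervention, baseline RSFC, age, and IQ as covariates".
- **Section 3.2** says of secondary analyses that "relationships between biomarkers and psychometric outcomes, and clinically defined subgroups will be considered exploratory". Section 2.7.3 sets the level: "All tests will use a two-sided 5% significance level".

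**The concern.** The hypothesis and the result to be replicated are both about change in connectivity. The planned analysis takes its connectivity measure from the post-intervention maps. On that measure, a child whose connectivity was high throughout looks the same as a child whose connectivity rose to that value during therapy.

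Two errors become possible. A real link between change in connectivity and change in communication can be missed, because stable between-child differences act as noise. A significant result can also arise with no such link, if children with a certain stable connectivity level tend to improve whichever therapy they receive. That second finding would concern who improves, and would not support the proposed mechanism of music therapy. What is at stake is the mechanistic hypothesis and the claim to have replicated it.

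**Working it through.** **1. The passages side by side.**

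| Place | Connectivity quantity | Baseline RSFC used? |
|---|---|---|
| Aims (hypothesis) | change | implied by change |
| Introduction (result to be replicated) | change | implied by change |
| 2.7.3, treatment comparison | post-intervention | yes, as covariate |
| 2.7.3, brain-behaviour regression | post-intervention | not stated |

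The within-participant model in 2.7.2 compares treatments on one outcome at a time. It does not define an association between two outcomes, so it does not supply the missing baseline term.

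**2. Inputs for the illustration.** The article plans no sample size for this analysis, so there is no figure of the plan's own to reproduce for it. The two-sided 5% level comes from 2.7.3. The rest are assumptions:

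- n = 70 children with usable pairs. This number is borrowed from the CCC-2 power calculation in 2.7.1, which reproduces: a paired t test with d = 0.34 and r = 0.50 has power 0.801 at n = 70. It is not stated as the number with usable scans.
- True correlation ρ = 0.40 between RSFC change and behaviour change.
- Retest correlation r of RSFC of 0.3, 0.5 or 0.7.
- Equal pre and post RSFC variances, with one row per child.

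**3. How well the post level stands in for change.** With equal variances, corr(post, post − pre) = √((1 − r)/2). This gives √0.35 = 0.59, √0.25 = 0.50 and √0.15 = 0.39.

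**4. If behaviour tracks RSFC change only.** The expected correlation of behaviour change with post RSFC is ρ√((1 − r)/2). Power uses Fisher's z: Φ(atanh(correlation) × √(n − 3) − 1.96), with √67 = 8.185.

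- Using change: atanh(0.40) = 0.4236; 0.4236 × 8.185 = 3.47; Φ(1.51) ≈ 0.93.
- Using post level at r = 0.5: atanh(0.20) = 0.2027; 0.2027 × 8.185 = 1.66; Φ(−0.30) ≈ 0.38.

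| r | Expected correlation, post level | Power, post level | Power, change |
|---|---|---|---|
| 0.3 | 0.24 | 51% | 93% |
| 0.5 | 0.20 | 38% | 93% |
| 0.7 | 0.15 | 25% | 93% |

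A simulation with 1,000,000 draws gave the same correlations.

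**5. If behaviour tracks a stable connectivity trait only.** Let pre and post each be the trait plus independent noise. Behaviour change correlates 0.40 with the trait and 0 with RSFC change. The expected correlation with post RSFC is 0.40√r, which is 0.22, 0.28 and 0.33. The post-level regression is then significant in about 45%, 66% and 81% of trials, although the hypothesised link is absent.

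**6. Adding baseline RSFC as a covariate.** The relevant quantity is the partial correlation of behaviour change with post RSFC given baseline RSFC.

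- Under step 4, with a = 0.40√((1 − r)/2), it is a(1 + r)/√((1 − a²)(1 − r²)) = 0.33, 0.35 and 0.37. This recovers most of the 0.40.
- Under step 5, with b = 0.40√r, it is b(1 − r)/√((1 − b²)(1 − r²)) = 0.16, 0.17 and 0.15. The trait signal shrinks from 0.22, 0.28 and 0.33 but does not vanish, because baseline is itself a noisy measure of the trait.

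**The case against.** **Ambiguity.** The sentence does not say which variable is dependent and does not exclude a baseline term. Its phrase about RSFC and behaviour change could mean change in both, and it follows an ANCOVA that does adjust for baseline. This stands in part. However, the simple association test is the same whichever variable is dependent, and the named input is explicitly the post-intervention maps. If change was meant, the sentence still needs correcting.

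**The post level is not uninformative.** On the figures above it correlates 0.39 to 0.59 with change. This stands. A reader might infer that the regression does not test the hypothesis at all, but the documents support only the weaker statement that the test is diluted and confounded.

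**The numbers are invented.** The correlations, the equal variances and the 70 usable pairs are not this trial's figures. This stands, and the loss of power is an illustration rather than a property of the trial.

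**Crossover, scanner and contrast handling.** A reader might also infer that the two post-intervention maps per child will be pooled as if independent, that scanner differences will be ignored, or that the music-minus-play contrast has been dropped. The article says none of this. It is silent, and a condensed article may leave such detail to the full plan.

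**Consequence.** Section 3.2 already calls such relationships exploratory. This stands and limits the weight of the point, but an exploratory analysis should still address the hypothesis it is attached to.

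**Conclusion.** The mismatch is real and lies between two things the article states, so it is not merely a missing detail. The hypothesis concerns change in connectivity, and the regression as written uses level after intervention. Followed literally, it can dilute a true change-change association and can be significant because of a stable trait alone.

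The size cannot be fixed from the documents. Under the stated assumptions the expected correlation falls from 0.40 to between 0.15 and 0.24. The direction depends less on the chosen values: with equal variances, post level correlates less than perfectly with change at any retest correlation above −1.

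Neither primary treatment comparison is affected. The correction is worth making before analysis, because changing the connectivity measure later would look post hoc.

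**What to change.** In 2.7.3, replace post-intervention RSFC in the brain-behaviour regression with within-period RSFC change (post minus pre), or keep post-intervention RSFC and add the matching baseline RSFC as a covariate. Relate it to CCC-2 change over the same period.

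The change score matches the hypothesis as worded. The covariate form is also acceptable, but removes a stable-trait effect only partly when RSFC is measured with noise (step 6 of the working). One acceptable crossover form relates the music-minus-play contrast of RSFC change to the same contrast of CCC-2 change, with one row per child. The Aims do not require that narrower version. Keep the exploratory label from 3.2.

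The cost is one sentence. No new data are needed, since assessments are already scheduled at all four time points; the trial was still recruiting when the article was written. The small downside is that change scores are noisier and need usable scans both before and after a period. The 93% therefore applies only if a correlation of 0.40 holds on the scale chosen.

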#### Psychometric outcomes

2.4.1.

Psychometric outcomes include: (1) social communication (primary); (2) participation; (3) family quality of life; (4) receptive vocabulary; (5) social functioning; (6) adaptive behavior; and (7) predictive processing. Participation and family quality of life are the two main secondary psychometric outcomes because of their particular importance to participants. All outcomes except social communication, receptive vocabulary, and predictive processing are parent-rated.

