#### Power calculation

2.7.1.

We designed M4A to be powered for an effect size of *d* = 0.34. Sharda et al. reported a mean difference of 4.84 and an effect size of *d* = 0.34 (SD not reported but calculated as 4.84/0.34 ≈ 14.2) on the CCC-2. Our previous Cochrane review showed similar effect sizes (81). We further assumed outcomes for MT and PT to be correlated with *r* = 0.50. With a two-sided significance level of 5%, a sample of *n* = 70 will be required for 80% power; to accommodate for attrition, we plan to recruit 80 participants. Similar power can be achieved for a range of reasonable effect sizes and correlations (Figure 3). The same power can be reached with varying combinations of effect sizes, correlations, and numbers of participants with complete data; in contrast, a parallel design would require almost 300 participants (Supplementary Table S2).

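### Bonferroni for the two main secondary outcomes is valid, but Holm's procedure would reject at least as often with the same 5% familywise guarantee: a cheap, optional improvement

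*Protocol article*

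**What the plan says.** Section 2.4.1 singles out two outcomes: "Participation and family quality of life are the two main secondary psychometric outcomes because of their particular importance to participants". They are the participation scale (CASP) and the family quality of life scale (FQoL), and neither is ranked above the other.

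Section 2.7.3 sets the level, "All tests will use a two-sided 5% significance level", and the adjustment, "The two main secondary psychometric outcomes, participation, and quality of life will be Bonferroni-corrected". The other secondary outcomes are labelled exploratory there. No order or weighting is given, and no reason for a single-step rule.

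Section 2.7.1 sizes the trial on the primary outcome alone: "We designed M4A to be powered for an effect size of *d* = 0.34", and "We further assumed outcomes for MT and PT to be correlated with *r* = 0.50". This leads to 70 participants for 80% power at two-sided 5%, with 80 to be recruited. No effect size or power is given for CASP or FQoL.

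**The concern.** Bonferroni tests both outcomes at 2.5% whatever happens. Holm tests the smaller p-value at 2.5% and, if that is rejected, the larger at 5%. With p = 0.01 and p = 0.04, Bonferroni declares one outcome and Holm declares both. Both procedures carry the same familywise guarantee of 5%.

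Section 1.1 hypothesises improvement in both outcomes, which is the situation in which Holm helps. At stake is some power on two outcomes chosen for their importance to families. The validity of the trial's error control is not in question.

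**Working it through.** **Reproducing the plan's sample size.** Inputs from section 2.7.1: d = 0.34, r = 0.50, two-sided 5%, 80% power.

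- The SD of the within-participant difference is SD × √(2(1 − 0.50)) = SD, so the paired effect size is also 0.34.
- Normal approximation: ((1.960 + 0.842)/0.34)² = 67.9, so 68.
- Noncentral paired t: n = 70, power 80.1%. The stated 70 is reproduced.

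**Cost of testing at 2.5%.** Assumption, not in the article: CASP and FQoL also have a paired effect of 0.34. At n = 70, power is 80.1% at 5% and 70.9% at 2.5%, a loss of 9.2 points. About 85 complete cases would restore 80% at 2.5%, more than the 80 to be recruited.

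**What Holm returns, independent outcomes.** Let a be the power at 5% and b the power at 2.5%, equal for both outcomes.

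- Per outcome: b + (a − b) × b = 0.709 + 0.092 × 0.709 = 0.774.
- Both, Bonferroni: b² = 0.709² = 0.503.
- Both, Holm: a² − (a − b)² = 0.801² − 0.092² = 0.633.
- At least one, either procedure: 1 − (1 − b)² = 1 − 0.291² = 0.915.

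**Correlated outcomes.** Simulated paired t statistics, n = 70, 400,000 replicates per setting. The correlation between outcomes is also an assumption.

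| Correlation | Per outcome, Bonferroni | Per outcome, Holm | Both, Bonferroni | Both, Holm | At least one, either |
|---|---|---|---|---|---|
| 0 | 71.0% | 77.5% | 50.3% | 63.3% | 91.6% |
| 0.3 | 71.0% | 76.9% | 54.1% | 65.9% | 88.0% |
| 0.5 | 71.0% | 76.5% | 56.7% | 67.7% | 85.2% |
| 0.8 | 71.0% | 75.6% | 62.1% | 71.3% | 79.8% |

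A normal-theory simulation with power set to exactly 80% at 5% agrees. For correlations 0 to 0.5 it gives 71.2% against 76.4-77.5% per outcome, and 50.7-57.1% against 63.2-67.6% for both.

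**Smaller effects.** The gain per outcome under independence is (a − b) × the other outcome's power at 2.5%. Normal approximation, critical values 1.960 and 2.241:

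| Power at 5% | Power at 2.5% | Gain per outcome |
|---|---|---|
| 80%, both outcomes | 71.2% | 0.088 × 0.712 = 6.2 points |
| 50%, both outcomes | 38.9% | 0.111 × 0.389 = 4.3 points |
| 30%, both outcomes | 21.0% | 0.090 × 0.210 = 1.9 points |
| 80%, the other outcome null | 71.2% | 0.088 × 0.025 = 0.2 points |

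**Error rates.**

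- Both nulls true: the familywise error is the same for the two procedures, 4.9% at correlation 0 and 4.1% at 0.8 (n = 70).
- One null true: that outcome's false-positive rate is 2.5% under Bonferroni. Under Holm, with independent outcomes, it is 0.025 + 0.025 × 0.709 = 4.3% at n = 70. With 80 complete cases it is 0.025 + 0.025 × 0.774 = 4.4%. Holm's bound is 5%.

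**Intervals.** Holm differs from Bonferroni only when the larger p-value lies above 0.025 and at or below 0.05, the smaller being at or below 0.025. In each such case the 97.5% interval for that outcome includes zero although Holm rejects.

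**The case against.** The strongest reply is that nothing here is wrong. Section 2.7.3 names a valid, unambiguous rule for a defined family, and choosing a single-step rule is a matter of efficiency. That stands, and it is why the point is an optional improvement.

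Four readings go further than the article supports.

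- **That Bonferroni is an error, or leaves error control deficient.** It controls the familywise error at 5%, and is the stricter rule when only one outcome has a real effect.
- **That Holm's error rate is identical.** The two agree when both nulls are true. With one true null they differ, 2.5% against about 4.3-4.4%, both within the 5% limit.
- **That the trial loses several points of power on each outcome whatever the truth.** The effect of 0.34 belongs to the primary outcome. Section 3.2 says that power was calculated for the primary outcomes, so the loss for CASP and FQoL depends on effects the article does not give.
- **That Bonferroni is inferior in every respect.** This holds for rejections only. Bonferroni tests match 97.5% simultaneous intervals; Holm's additional rejections never do.

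Section 3.2 also calls analyses of secondary outcomes exploratory. That lowers the importance of the point. It does not remove it, because section 2.7.3 reserves that label for the remaining secondary outcomes and gives these two a formal correction. Finally, section 5 reports 53 participants randomised by June 2023, so this would be a mid-trial relaxation of a multiplicity rule. That is defensible only if it is made without sight of comparative data.

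**Conclusion.** The point holds as a low-priority efficiency improvement. For two unranked outcomes, Holm gives the same strong 5% familywise guarantee and never rejects less. The benefit is a better chance on the second outcome after the first has succeeded: 4.5 to 6.5 points per outcome and 9 to 13 points for showing both, at n = 70 with both paired effects at 0.34 and correlation between outcomes from 0.8 down to 0. These figures rest on an assumed effect and an assumed correlation. The gain shrinks with smaller effects and nearly vanishes if only one effect is real. The sample size and the primary analyses are unaffected.

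**What to change.** Optional. In section 2.7.3, change Bonferroni-corrected to Holm-corrected (two-sided familywise 5%) for participation and family quality of life. Record it as a dated, justified protocol change, listed with the others in Supplementary Table S1 and made before anyone sees comparative data on these outcomes. If that can no longer be assured, keep Bonferroni.

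Report Holm-adjusted p-values for both outcomes. If 97.5% simultaneous intervals are also given, say in advance that an interval may include zero for an outcome rejected at the second step.

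The wording change is small, and no new data or participants are needed. The costs are the amendment, the higher false-positive rate when one null is true, and the loss of a one-to-one match between tests and intervals.
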